### Statistical analysis

The primary hypothesis will be addressed using a mixed linear regression analysis with robust variance estimation, assessing the frequency of NSSI within the past 3 months at T0 and T2. We will consider main and interaction effects of the two main effects: (1) group allocation; and (2) time of assessment within repeated measures. The individuals’ ID will be used as random effect variable. In secondary analyses, potential sociodemographic and clinical mediators and predictors of intervention response will be investigated. Missing data and individuals withdrawn from the trial will be handled using an intention-to-treat (ITT) approach. All participants randomized will be considered in the analyses. In the case of drop-outs or missing data, we will use a last-value-carried-forward imputation method, assuming that those who dropped out of the intervention showed no improvement in NSSI relative to baseline.

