### Objectives and outcomes

The main objective of the present study is to evaluate a newly developed, easily accessible, online intervention program for adolescents and young adults engaging in NSSI, based on an existing short-term face-to-face manualized intervention (CDP). The effectiveness of online CDP will be evaluated in a RCT in comparison to an online psychoeducation program. The main outcome of the trial is the reduction in the frequency of NSSI within the last three months assessed by the NSSI Severity Questionnaire (NSSV-SG) [33] at one-year follow-up (primary endpoint; T2).

Secondary outcome criteria are health-realted quality of life as well as comorbid psychopathology and suicidal behavior.

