### Inclusion and exclusion criteria

Based on the criterion A of the NSSI disorder provided in the *Diagnostic and Statistical Manual of Mental Disorders* (DSM), fifth edition, section three [3], eligible participants are required to have engaged in NSSI on at least five days during the last 12 months. Eligible participants are aged 15–21 years. Furthermore, all participants need to provide informed consent online by clicking a checkbox. Participants will be excluded if they are currently receiving individual psychotherapy (inpatient and outpatient).

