### Sample size

Power analysis was based on reported effect sizes of CBT in the reduction of NSSI, drawing on the most extensive meta-analysis in the field [52] reporting a main effect for the reduction of NSSI in *n* = 8/14 studies; g = − 0.27, 95% CI [− 0.17, 0.38], z = 4.96, *p* = 0.001). Most studies included in the analysis used a treatment as usual (TAU) control group design. Comparing online CDP against an online psychoeducation we expect similar effects. Power analysis was calculated for F-statistics using an alpha-error probability of 0.05. The estimation model was based on a mixed effect linear regression with main effects (repeated measures and group) and their interaction. We considered covariates with potential impact on the outcome (sex, age). Based on the calculation, a minimum sample size of *n* = 344 is necessary to reveal significant effects at a critical F-value of F = 1.859. Based on this estimation, the study would allow for up to 51% drop-out and still be sufficiently powered revealing effects in a completer analysis.

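### The primary contrast is an unadjusted difference in raw change of a probably skewed, floor-bounded NSSI frequency: valid, but likely inefficient, and mainly repairable by conditioning on baseline

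*Protocol article*

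**What the plan says.** The protocol article's Objectives and outcomes section defines the main outcome as the "reduction in the frequency of NSSI within the last three months assessed by the NSSI Severity Questionnaire (NSSV-SG") at T2, one year after baseline. The Statistical analysis section assigns to it a "mixed linear regression analysis with robust variance estimation, assessing the frequency of NSSI within the past 3 months" at T0 and T2. On the contrast it states: "We will consider main and interaction effects of the two main effects: (1) group allocation; and (2) time of assessment within repeated measures". The participant's "ID will be used as random effect variable". No transformation, link function or count model is named, and baseline frequency enters as a response, not as a covariate. Missing values are filled by carrying the last value forward.

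Under Inclusion and exclusion criteria, participants are "required to have engaged in NSSI on at least five days during the last 12 months". No upper limit is stated.

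On planning, the Sample size section says: "Power analysis was calculated for F-statistics using an alpha-error probability of 0.05". It assumes a standardized effect of g = 0.27 under the same kind of linear mixed model, with sex and age as the covariates considered, and arrives at 344 participants at a critical F of 1.859. No mean, standard deviation, share of zeros or distribution of NSSI frequency appears anywhere in the article.

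**The concern.** Two features of the contrast cost precision on an outcome of this kind.

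First, a raw change score subtracts the whole baseline value. When baseline and follow-up are only moderately correlated, and the spread shrinks as the mean falls, this adds noise that a baseline covariate would remove.

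Second, the eligible population runs from people who self-injure about once in three months to people who may do so daily. On the raw scale the first group can hardly move and the second can move by dozens of days, so a few heavy users carry most of the variance. Robust standard errors protect the type I error. They neither restore the lost precision nor reduce the weight of extreme values.

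The stake is a false-negative primary result. The Limitations section expects 50% attrition by T2, which leaves about 700 × 0.5 / 2 = 175 completers per arm and little room for an inefficient primary analysis.

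**Working it through.** **The plan's own figure.** A noncentral-F calculation with f = 0.27 (f² = 0.0729), 10 numerator degrees of freedom, alpha 0.05 and 95% power gives N = 344 and a critical F of 1.859, matching the article. The 10 degrees of freedom, the 95% power and the use of g as Cohen's f are inferred from the match, not stated. No distribution enters, so 344 says nothing about skew.

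**Floor and range.** Five days in 12 months is 5 × 91/365 = 1.25 days per three months. A participant at that rate has a chance of exp(−1.25) = 0.29 of reporting none in a given three months (Poisson). A daily self-injurer can fall by about 90.

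**What change scoring costs.** With both values present for everyone, group by time with a participant intercept equals the difference in mean (T2 − T0). Let σ0 and σ2 be the standard deviations at T0 and T2, ρ their correlation and k = σ2/σ0.
- Variance of the change: σ0² + σ2² − 2ρσ0σ2.
- Residual variance with baseline as covariate: σ2²(1 − ρ²).
- Ratio: (1 + k² − 2ρk) / [k²(1 − ρ²)].

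Take k = 0.7 (spread falls with the mean by an assumed 30%). With ρ = 0.42 the ratio is 0.902/0.404 = 2.2; with ρ = 0.61 it is 0.636/0.308 = 2.1. The change score then needs about twice the sample before any question of scale arises.

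**Total N for 80% power.** Assumed data: days of NSSI in 91, log-normal personal rates, entry rule applied, 30% fall in both arms. N per arm = 2(1.960 + 0.842)²/d² = 15.7/d². Example with median 8, log-SD 1.0, latent correlation 0.5:

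| Effect | Raw change | Raw, baseline covariate | Log(1+y) change | Log(1+y), baseline covariate |
|---|---|---|---|---|
| Rate ratio 0.7 in all (d) | 0.193 | 0.295 | 0.295 | 0.349 |
| Total N | 846 | 362 | 362 | 258 |
| Ratio 0.6, above-median users only (d) | 0.170 | 0.272 | 0.211 | 0.260 |
| Total N | 1088 | 424 | 708 | 464 |

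Seven parameter sets were tried (median 4-15, log-SD 0.6-1.3, correlation 0.5-0.7).
- Raw change needs 2.0 (1024/516) to 2.7 (592/222) times the N of the raw model with baseline under a proportional effect, and 2.2 to 2.7 times under the heavy-user effect.
- The raw model with baseline needs 1.1 (102/92) to 1.6 (546/348) times the N of the log model with baseline under a proportional effect. Under the heavy-user effect it needs less, at 0.70 (268/382) to 0.93 (564/608) times.

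**Simulated power, 175 completers per arm, rate ratio 0.70, 40% fall in control.** Overdispersed counts, heteroscedasticity-robust standard errors:

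| Assumed data | Raw change | Raw, baseline covariate | Log(1+y), baseline covariate |
|---|---|---|---|
| Strong skew: baseline mean 12, SD 21, log-SD 1.1, correlation 0.55 | 18% | 51% | 71% |
| Less skew: log-SD 0.7, capped at 91 | about 34% | 85% | 89% |
| Benefit only in above-median users, capped at 91 | about 13% | about 30% | about 30% |

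Under proportional effects the log model with baseline spans 69-89%. Rejection under the null was about 5% for all methods. In the strong-skew case log change alone also gives 51%, so either repair by itself gains 33 points and the second adds 20. In that case the most extreme 5% of participants (18 of 350) carried 63-76% of the variance of the raw change score.

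**The case against.** The strongest reply is that the plan's contrast answers the stated hypothesis directly. A greater reduction in frequency is a difference in mean change, which under randomization needs no constant additive effect, and robust variance keeps the test honest. That stands: the fault is one of efficiency and sensitivity to extremes, not validity, and a rate ratio answers a somewhat different question.

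It is also fair that the protocol supplies no distribution and no scoring rule. The Assessment measures section says only that the 60-item questionnaire covers frequency and nature of NSSI. If frequency is scored in ordered classes, the count arithmetic falls away. A transformation might also be specified in an analysis plan not shown, so that the outcome is untransformed is an inference from what is named. The contrast, however, is written into the article.

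A reader might infer that the linear scale alone explains the gap, for example 18% against 71%. The figures do not support that, because the comparison changes two things at once: scale and baseline adjustment. Staying linear and adding baseline recovers 33 of the 53 points. With less skew the scale adds little more (85% against 89%), and with benefit confined to heavy users it adds nothing.

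A reader might also take 18% as the power of the planned primary analysis. That is not supported either: the simulations use completers, whereas the plan analyses all randomized participants with the last value carried forward.

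**Conclusion.** The point holds as one about efficiency. An unadjusted raw change contrast on an outcome that is probably skewed and bounded at zero is valid but likely wasteful, and it leans on the heaviest self-injurers. It was the least efficient of the analyses compared in every scenario examined.

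The direction is firm for baseline adjustment, which roughly halves the required sample across the assumptions tried, whether the effect is proportional or confined to heavy users. The further gain from a relative scale depends on a proportional effect and marked skew, and it can reverse. All magnitudes rest on assumed distributions, correlations and falls over time. None can be computed from the protocol.

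**What to change.** 1. Replace the raw change contrast by the group difference at T2 conditional on baseline frequency. Either use analysis of covariance, or a mixed model with baseline means constrained equal across arms and separate variances at T0 and T2. Keep robust standard errors. This retains the absolute effect measure and needs no new data, because frequency is already measured at T0.
2. State how the NSSV-SG frequency item is scored. If it is a count of days or acts, prespecify a negative-binomial log-link model with log baseline frequency and robust standard errors, reporting a rate ratio, as the primary or a key supporting analysis. Report the absolute mean difference alongside. If frequency is scored in classes, use an ordinal model.
3. If log(1+frequency) is used, report the exponentiated coefficient as a ratio of geometric means of (1+frequency). It is not a rate ratio, least of all near zero.
4. Fix these choices before outcome data are seen.

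The cost is analysis wording only. The one downside is that making a relative-scale model primary changes the effect measure from an absolute difference to a ratio, so the primary hypothesis would need matching wording. Item 1 alone avoids that.

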### Data assessment

All assessments will be conducted online. Thus, self-report questionnaires will be used in this trial. The assessment at T0 takes place before randomization and the subsequent start of treatment. All assessment measures are conducted at every time point (T0, T1, T2, T3), except the evaluation of the online CDP, which only takes place at T1. Within a first screening phase of T0, participants are checked for eligibility. All eligible participants are invited to participate in the trial. Those not eligible for the trial because of current individual psychotherapy and/or too low frequency of NSSI are invited to participate in a separate non-interventional observational study.

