### Assessment measures

T0 comprises sociodemographic questions, which will gather information about gender, nationality, state of adolescents’ and parents’ education, and current living situation.

For detailed assessment of NSSI severity, we use the NSSV-SG [33], assessing the frequency and nature of NSSI within the past three months using 60 items. The evaluation of the psychometric properties in a clinical and an online sample of adolescents and young adults indicates high internal consistency (Cronbach α = 0.73), a test–retest reliability of 0.77 (*n* = 29; interval: six weeks), and supports the validity of the questionnaire [34]. The *KIDSCREEN-10* will be used to assess general health-related quality of life (HRQoL) in participants [35]. It consists of 10 items and was developed across Europe for use in children aged 8–18 years and is a valid instrument with acceptable retest reliability [35]. Internal consistency was high (Cronbach α = 0.81) [36]. To assess emotional and behavioral difficulties in children and adolescents, the *Strengths and Difficulties Questionnaire* (SDQ) [37] with 25 items will be used. A study, evaluating the validity of the German version of the SDQ, indicates that the SDQ is valid for most clinical and research purposes [38]. In addition, the questionnaire shows good internal consistency (Cronbach α = 0.81) [39]. The *Borderline Symptom List-23* (BSL-23) [40] is a quantitative assessment of borderline-specific symptoms based on DSM-IV criteria [41]. It consists of 23 items and shows high internal consistency (Cronbach α = 0.94) [40]. The BSL-23 is a reliable and valid instrument to assess borderline-specific symptoms [40]. To assess personality disorders, the *Self-report Standardised Assessment of Personality* – abbreviated scale (SAPAS-SF) consisting of eight items [42] will be used. The SAPAS is a valid and reliable instrument to screen for personality disorders [42, 43]. The internal consistency coefficients were rather low, in the range of 0.35–0.51 [44]. The *Paykel Suicide Scale* (PSS) [45] assesses the intensity of suicidal behaviors by level of intent and consists of five items. The *Patient Health Questionnaire-9 for Adolescents* (PHQ-A) [46] is a modified version of the *Patient Health Questionnaire-9* (PHQ-9) [47]. The PHQ-9 measures depression severity and shows good internal consistency (Cronbach α = 0.84) [48]. The PHQ-A consists of nine items based on DSM-IV [41]. The PHQ-A is a reliable and valid measure of depression severity [46] and shows good.

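### The primary group-by-time contrast on T0 and T2 is a difference in mean change that does not adjust for the NSSI frequency already measured at baseline: valid, but generally less efficient than baseline adjustment

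*Protocol article*

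**What the plan says.** The Statistical analysis section of the protocol article commits the primary hypothesis to a "mixed linear regression analysis with robust variance estimation, assessing the frequency of NSSI within the past 3 months at T0 and T2". The fixed effects are given as "We will consider main and interaction effects of the two main effects: (1) group allocation; and (2) time of assessment", and the participant's "ID will be used as random effect variable". T0 therefore enters as a response value alongside T2. No baseline covariate is named.

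Everyone randomised is to be analysed. For gaps, "we will use a last-value-carried-forward imputation method, assuming that those who dropped out of the intervention showed no improvement in NSSI relative to baseline".

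The Procedure and randomization and Data assessment sections put the T0 assessment before randomisation and repeat every outcome measure at each visit, so baseline NSSI frequency is available for every randomised participant.

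The article gives no SDs and no correlation between T0 and T2. The nearest figure, under Assessment measures, is "a test–retest reliability of 0.77" for the NSSI questionnaire, from 29 people over six weeks.

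**The concern.** Randomisation makes the expected T0 means of the two arms equal. A model with a free group main effect does not use that fact: it estimates a baseline difference whose expectation is zero and subtracts it from the T2 difference. The noise in that baseline difference then stays in the treatment estimate. Using T0 as a covariate, or forcing a common T0 mean, estimates the same between-arm effect at T2, in general with smaller variance and from the same data.

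What is at stake is precision. The Limitations section expects half of the sample to be lost by T2, and the planning effect is small (0.27), so avoidable variance costs power.

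**Working it through.** **The plan's own figure.** The Sample size section gives a minimum of 344 at a critical F of 1.859. Both numbers are reproduced by an omnibus F-test with 10 and 333 degrees of freedom, f² = 0.27² = 0.0729 and 95% power. These degrees of freedom, f² and power are inferred from the match; the article does not state them. The calculation contains no T0–T2 correlation, so it does not settle the size of the present point.

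**Step 1: what the interaction estimates.** With two visits per person, complete data and a random intercept, the group-by-time coefficient is the arm difference in mean (T2 − T0). One simulated data set (350 per arm, ρ = 0.5) confirms this:

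- Mixed model and change-score regression: both −0.22882, SE 0.07735.
- Baseline-adjusted regression: SE 0.06804. The variance ratio is (0.06804/0.07735)² = 0.77, against 0.75 in theory.
- Mixed model without the group main effect (common T0 mean): SE 0.0664.

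**Step 2: variances.** In units of the T0 variance, with k the ratio of T2 SD to T0 SD:

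- change contrast: 1 + k² − 2ρk
- baseline-adjusted: k²(1 − ρ²)
- information lost: (1 − ρk)² / (1 + k² − 2ρk)

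At k = 1 these become 2(1−ρ), 1−ρ² and (1−ρ)/2.

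**Step 3: completers only, k = 1.** Inputs: d = 0.27 (Sample size section), two-sided α = 0.05, and 50% of 700 = 350 with T2 observed, or 175 per arm (Limitations). The values of ρ are assumed, except 0.77. Power ≈ Φ(d√(n/2)/√v − 1.96). At ρ = 0.5, 0.27 × √87.5 = 2.526. The change contrast has v = 1, giving Φ(0.566) = 71%. The adjusted contrast has v = 0.75, giving 2.526/0.866 = 2.916 and Φ(0.956) = 83%.

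| ρ | 2(1−ρ) | 1−ρ² | Loss | Power, change | Power, adjusted |
|---|---|---|---|---|---|
| 0.3 | 1.40 | 0.91 | 35% | 57% | 75% |
| 0.5 | 1.00 | 0.75 | 25% | 71% | 83% |
| 0.6 | 0.80 | 0.64 | 20% | 80% | 88% |
| 0.77 | 0.46 | 0.407 | 11.5% | 96% | 98% |

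**Step 4: the planned analysis, all 700 with values carried forward.** Assume that half have T0 carried to T2, with no common time trend. The correlation in the filled data becomes ρ* = 0.5 + 0.5ρ, the mean effect halves to 0.135, and n is 350 per arm. At ρ = 0.5, ρ* = 0.75 and 0.135 × √175 = 1.786. The change contrast gives 1.786/√0.50 = 2.526, or 71%. The adjusted contrast gives 1.786/√0.4375 = 2.700, or 77%.

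| ρ in completers | ρ* | Loss | Power, change | Power, adjusted |
|---|---|---|---|---|
| 0.3 | 0.65 | 17.5% | 57% | 65% |
| 0.5 | 0.75 | 12.5% | 71% | 77% |
| 0.6 | 0.80 | 10% | 80% | 84% |
| 0.77 | 0.885 | 5.75% | 96% | 97% |

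A simulation of this setting (3,000 trials per value) gave 56 vs 64%, 72 vs 78%, 81 vs 85% and 96 vs 96%.

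**Step 5: unequal SDs among completers.** At k = 0.8 the loss runs from 36% (ρ = 0.77) to 49% (ρ = 1/3). At k = 1.2 it runs from 1% to 22% over the same values.

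**The case against.** The planned contrast is a standard, prespecified choice, it is unbiased under randomisation, and it matches a hypothesis worded as a greater reduction. All of that is true. It does not defeat the point, because baseline adjustment targets the same between-arm effect under randomisation and needs no further data.

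The stronger part of the objection concerns size, and most of it stands. A reader might infer any of the following, and the article does not support them:

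- **A quarter to a third of the information is wasted.** That needs ρ between 1/3 and 1/2 and equal SDs. Neither is reported. The six-week retest value probably overstates a 12-month correlation, but it does not say by how much.
- **The completer power gains (18, 12 and 8 points) apply to this trial's primary analysis.** The Sample size section mentions a completer analysis only to describe how much drop-out can be tolerated. The primary analysis covers all randomised participants with values carried forward, and there the gains are about half as large or less.
- **The planned test is worse than ignoring baseline.** With equal SDs this is so among completers when ρ is below 0.5. With half the values carried forward from T0, ρ* is at least 0.5 for any non-negative ρ, so under that assumption it does not apply to the planned analysis.
- **Chance baseline imbalance biases the result.** It does not under randomisation. Within a given trial, with equal SDs, only the fraction 1−ρ of an imbalance enters, with reversed sign.
- **The primary model contradicts the sample-size section over sex and age.** The Statistical analysis section does not exclude these covariates, and an article may leave the covariate list to a fuller plan. Adding them as main effects leaves the interaction in this two-visit model unchanged.

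**Conclusion.** The structural point holds on the article's own text: the primary contrast is an unadjusted difference in mean change, and it does not condition on a baseline value that is in hand for everyone. This costs efficiency and introduces no bias or invalidity.

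The size can only be given as a range. With equal SDs, the loss among completers is 11.5% to 35% for ρ from 0.77 down to 0.3. In the planned analysis it is about 6% to 17.5% if T0 is carried forward for half of the sample. The power gain there is about 8 points at ρ = 0.3 and about one point or less at 0.77.

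These figures rest on assumed correlations, equal SDs, d = 0.27 among completers, 50% missing at T2, and T0 as the value carried forward. Carrying T1 values for those lost between T1 and T2 would change them somewhat. So would an SD that rises or falls after baseline. The change is worth making because it is nearly free; the trial's validity does not depend on it.

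**What to change.** In the Statistical analysis section, replace the group-by-time specification of the primary test with one of two equivalent-in-aim models:

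- a linear regression of T2 NSSI frequency on group, with T0 NSSI frequency as covariate and robust variance; or
- a longitudinal model in which both arms share a common T0 mean and group enters only after baseline.

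State that the primary test is the one-degree-of-freedom group contrast at T2. The unadjusted change contrast can stay as a supporting analysis.

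The cost is one sentence, recorded before outcome data are analysed and notified through the amendment and registry route that the article already describes. No extra data, visits or participants are needed, and the hypothesis is unchanged.

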## Background

Non-suicidal self-injury (NSSI) affects approximately 17–18% of adolescents worldwide [1, 2]. NSSI is characterized by the intentional and self-inflicted destruction of body tissue without suicidal intent [3]. The importance of NSSI is highlighted by recent research illustrating that NSSI is an important predictor of suicidal behavior [4–6]. Furthermore, it is highly associated with other risk-behaviors and comorbid psychopathology [7, 8]. NSSI is a common and highly recurrent behavior that peaks in adolescence [4, 9–11].

It is essential to develop interventions supporting adolescents with NSSI to stop the behavior. However, only few interventions have been developed that specifically target NSSI despite its high clinical pertinence [12–14]. NSSI, particularly in the context of (emerging) borderline personality disorder (BPD), is often treated with Dialectical Behavior Therapy for adolescents (DBT-A), which has shown to be effective [15]. Other treatments that seem effective for reducing NSSI frequency are Mentalization-Based Treatment for adolescents (MBT-A) as well as Cognitive Behavioral Therapy (CBT) [16, 17]. A recent meta-analysis [16] suggested that DBT, MBT, and CBT may all be effective for treating NSSI. However, comprehensive access to these treatments is restricted due to limited resources and a lack of specially trained clinicians [18]. Given the limited resources in the mental healthcare field, it remains a matter of discussion if DBT-A and MBT-A, which are targeted at youth with BPD need to be fully implied.

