## Methods/Design

### Setting and recruitment

The present trial is a study within the consortium “Self-injury-Treatment: Assessment, Recovery (STAR).” Cooperating study sites (Ulm, Landau, Mannheim, Karlsruhe, and Berlin) will investigate the natural course of NSSI as well as psychocological and neurobiological predictors and improve ways to dessiminate specific knowledge on NSSI to primary caregivers.

We aim to include *n* = 700 adolescents and young adults aged 15–21 years in the trial. They will be randomly assigned to either receive the online CDP or online psychoeducation only. Participants in both groups will be assessed at the beginning (baseline; T0), 4 (post-line; T1), 12, and 18 months after the initial baseline assessment (follow-up; T2, T3) in order to evaluate treatment effects. The flowchart of the trial is shown in Fig. 1. The schedule of this trial is shown in Fig. 2 (Additional file 1).

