To prevent bias, participants will be randomly assigned to receive either the online psychoeducation or the online CDP using block randomization (50/50). Participants will be randomized based on their study ID. Enrolment, generation of allocation sequence, and assignment of participants take place online and are therefore computer-based. Participants will be informed about their group affiliation by automatic message that pops up immediately after randomization. Blinding is not completely possible. Participants cannot be blinded due to the different nature of the interventions. Blinding of the researchers is not possible, because participants in the online CDP group receive case-management and personal chats as well as telephone calls.

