## Limitations

Despite the mentioned advantages, potential limitations of the study design should be acknowledged. Participant drop-out is a potential challenge, particularly given the online nature of the intervention. Based on a Cochrane Review [58], attrition rates from 4% [59] up to 21% [60] were reported within face-to-face treatments of adolescent self-harm (including NSSI). Concerning online interventions for adolescents with diagnoses of depression [61, 62] and anxiety [61, 63], drop-out rates from 6% [64] up to 31% [65] were reported. Considering the mentioned studies, an attrition rate of 30% to T1 and 50% to T2 is expected, expecting *n* = 504 adolescents to complete the intervention. The study is suitably powered even down to a completer sample of *n* = 344 adolescents.

Another potential limitation is that all participants will be able to access alternative treatments outside of the trial. Information will be collected from participants about menthal health service usage and the potential impact of this on outcomes will be statistically controlled for.

In addition, we are not able to diagnose mental disorders because of the exclusive use of surveys. This is due to the online character of the study.

The provision of an online intervention, tailored to the needs of adolescents and young adults, may provide an easily accessible, cost-effective, and flexible medium for improving mental health outcomes for affected individuals.

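### Carried-forward imputation of about half the primary T2 values is ambiguously specified, shrinks a lasting effect on either reading, and can create a false effect if drop-out is unequal or a T1 effect fades

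*Protocol article*

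**What the plan says.** Under Statistical analysis, the primary hypothesis is tested by a mixed linear regression of three-month NSSI frequency at T0 and T2, with group, time and their interaction, a random effect for the individual, and robust variance. Everyone randomised is to be analysed. Missing data and drop-out are handled by a "last-value-carried-forward imputation method, assuming that those who dropped out of the intervention showed no improvement in NSSI relative to baseline".

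Under Limitations, "an attrition rate of 30% to T1 and 50% to T2 is expected". The target under Setting and recruitment is "We aim to include *n* = 700 adolescents and young adults", allocated 1:1. Data assessment has every outcome measure collected at T0, T1, T2 and T3, so a T1 value of the primary variable exists for anyone who answers at T1. T1, at four months, is the end of treatment. T2, at twelve months, is the primary endpoint.

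Under Sample size, "a minimum sample size of *n* = 344 is necessary to reveal significant effects at a critical F-value of F = 1.859". The tolerance for drop-out given there refers to an analysis of completers. The article names no other missing-data method.

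**The concern.** When half the values of the primary endpoint are expected to be missing, the rule that fills them largely determines the primary result. Three features deserve attention.

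- **The method and its stated assumption agree only for some participants.** Someone lost before T1 has only a baseline value, so carrying the last value does mean no improvement. Someone who answers at T1 and misses T2 has a later value that may already show improvement.
- **Carrying a value forward fixes an outcome for the person.** Any true treatment effect at T2 among the missing is replaced by zero or by the end-of-treatment effect.
- **The filled values depend on who leaves.** If NSSI frequency changes over the year in both arms, the arm that loses more people shows less change. The Background says that "NSSI is a common and highly recurrent behavior that peaks in adolescence", which makes change over a year plausible without giving its size. Retention could differ by arm, since online CDP offers weekly case-manager contact and group chats while the control is static content.

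At stake are the size of the reported one-year effect, whether it reflects persistence to one year or the state at four months, and, in some scenarios, the false-positive rate.

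**Working it through.** **The plan's own figure.** 1 − 344/700 = 50.9%, which reproduces the article's 51% tolerated drop-out. Expected attrition of 50% leaves 350 observed at T2.

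**Who carries what.** Taking 30% and 50% as cumulative:
- T2 observed: 700 × 0.50 = 350
- T1 but no T2: 700 × (0.70 − 0.50) = 140, which is 40% of the missing
- baseline only: 700 × 0.30 = 210

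Limitations also gives 504 people completing the intervention, which is 72% of 700 rather than 70%. With 504 seen at T1 the split would be 154 and 196. This changes little below.

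**Expected contrast.** Effects are in SD units, positive when online CDP reduces NSSI more. Drop-out is equal by arm and completely at random.
- T1 carried where available: 0.20 × (T1 effect) + 0.50 × (T2 effect)
- T0 carried: 0.50 × (T2 effect)

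| Scenario | T1 carried | T0 carried |
|---|---|---|
| T1 = 0.27, T2 = 0.27 | 0.054 + 0.135 = 0.189 | 0.135 |
| T1 = 0.35, T2 = 0.27 | 0.070 + 0.135 = 0.205 | 0.135 |
| T1 = 0.27, T2 = 0 | 0.054 | 0 |
| T1 = 0.35, T2 = 0 | 0.070 | 0 |

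The 0.27 is the planning effect in the Sample size section. The T1 effects are assumptions. Relative to 0.27, the loss is 30% (0.189), 24% (0.205) or 50% (0.135).

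**Rejection rate when a T1 effect has faded (T1 carried, 350 per arm, two-sided 5%).** The variance of a person's change is 2(1 − r) if a later value is used and 0 if baseline is carried. The small contribution from the difference in means is ignored.
- T1 = 0.27, all correlations 0.5: variance 0.70 × 1.0 = 0.70; SE = √(2 × 0.70/350) = 0.063; 0.054/0.063 = 0.85; rejection about 14% (simulation 13%).
- T1 = 0.27, all correlations 0.7: variance 0.70 × 0.6 = 0.42; SE = 0.049; ratio 1.10; rejection about 20% (simulation 19%).
- T1 = 0.35, correlations 0.55 (T0–T1) and 0.45 (T0–T2): variance 0.20 × 0.90 + 0.50 × 1.10 = 0.73; SE = 0.065; ratio 1.08; rejection about 19% (simulation 19%).

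With T0 carried, simulated rejection in the faded scenarios is about 5%.

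**Unequal drop-out under a true null.** Assume both arms improve by 0.5 SD of change and T0 is carried. For an arm with a proportion q observed, the mean change is 0.5q and the variance is q + 0.25q(1 − q).
- 45% v 55% drop-out: bias 0.5 × (0.55 − 0.45) = 0.05; SE = √((0.612 + 0.512)/350) = 0.0567; ratio 0.88; rejection about 14%.
- 40% v 60%: bias 0.10; SE = √((0.66 + 0.46)/350) = 0.0566; ratio 1.77; rejection about 42%.

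With T1 carried, drop-out by T1/T2 of 20%/40% in one arm and 40%/60% in the other gives a simulated bias of 0.10 SD and 34% to 50% rejection (correlations 0.5 to 0.7). The sign follows retention: it favours online CDP if that arm is better retained and the control if not.

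**Where nothing goes wrong with the error rate.** With equal drop-out, a shared 0.5 SD improvement and no effect at T1 or T2, simulated rejection is 4.5% to 5.6% on both readings.

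**Power.** Attenuation does not translate directly into lost power. With an effect of 0.27 at T1 and T2 and correlation 0.5, simulated power is 85% with T1 carried, 71% with T0 carried and 73% for completers. The damage in that case is to the estimate and its confidence interval.

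**The case against.** The strongest defence is that the wording can be read consistently. The primary model contains only T0 and T2, so the last value within that model is T0, and carrying it is exactly an assumption of no improvement. Alternatively, the assumption is worded for people who left the intervention, which ends at T1, and those lost before T1 have only a baseline value. This stands: a reader might infer a flat contradiction between rule and assumption, but the article supports only an ambiguity. The faded-effect route likewise exists only if T1 is the value carried.

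A reader might also infer that the type I error is simply not 5%. That is too strong. Inflation needs a T1 effect that fades, with T1 carried, or unequal drop-out together with a shared trend. With equal drop-out and a lasting effect, the estimate is biased towards no difference.

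Nor does the planned model already solve the problem by itself. Fitted without imputation it would keep everyone, because T0 precedes randomisation, but it does not use T1 and so cannot draw on the best available information about those missing at T2.

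Finally, the article gives no arm-specific attrition, no one-year trend and no correlations, and it describes the same reminders for all participants. The larger percentages are therefore illustrations. An unseen analysis plan may add sensitivity analyses, and their absence here is not the point. What the defence leaves untouched is that single imputation by carrying values forward is the stated method, with half the primary values expected to be missing, and that it distorts the estimate on both readings.

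**Conclusion.** The point holds as a defect in a stated rule. Two conclusions apply whichever value is carried. A lasting effect of 0.27 SD is reported as about 0.19 to 0.21 (T1 carried, T1 effect 0.27 to 0.35) or 0.135 (T0 carried). Unequal drop-out combined with a shared change over time moves a true null towards the arm with better retention; with baseline carried and an assumed 0.5 SD improvement, rejection is 14% at 45% v 55% drop-out and 42% at 40% v 60%.

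A third conclusion is conditional. If T1 is carried, the stated assumption is not met for about 140 of the 350 missing values, and a T1 effect of 0.27 to 0.35 SD that has vanished by T2 yields a spurious 0.05 to 0.07 SD with about 13% to 19% rejection.

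The 140 and 350 follow from the article's own attrition figures read as cumulative. All effect sizes after imputation and all rejection rates rest on assumed correlations, T1 effects, trends and drop-out patterns, on normally distributed outcomes in the simulations, and on drop-out at random within arm.

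**What to change.** Replace carried-forward imputation in the primary analysis with a likelihood-based mixed model fitted to all observed values of all randomised participants. Extend it from T0 and T2 to include T1, treat time as categorical, and take the group contrast at T2 as the primary estimate. This is valid under missing at random given the observed T0 and T1 values.

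Keep no improvement from baseline, if wanted, as a sensitivity analysis explicitly labelled baseline carried forward, so that the value carried is no longer open to interpretation. Because missing at random cannot be verified with half the endpoint missing, add a missing-not-at-random analysis, such as delta-adjusted or reference-based multiple imputation.

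The cost is revised wording and a few more model runs. T1 is already collected, so no new data are needed. The price is that the primary estimate then relies on missing at random, which is why the sensitivity analyses belong with it.
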